### Outcome measures

#### Primary outcome measures

##### Children’s dietary intake

Children’s dietary intake is evaluated through an online 24-h food recall developed for this study (*SmartKidsDiet24*). Parents are asked to record all the foods eaten by the child in their presence, foods eaten in meals prepared or offered by parents (e.g., snacks sent to school), or foods that parents are sure that the child ate in the specific days chosen by the app. Foods offered by childcare facilities are not recorded. The app guides parents in registering food and portions for the five main meals (breakfast, morning snack, lunch, afternoon snack, dinner), but it is possible to add an extra meal or snack. Parents also report the time (hh:mm) the food or meal was eaten. The *SmartKidsDiet24* uses an electronic food composition database developed by INSA (National Institute of Health Doutor Ricardo Jorge), compiling several food information sources (i.e., analytical studies, scientific literature, label information, other food composition tables, nutritional composition calculation for specific recipes according to the EuroFIIR method) adapted to the Portuguese diet. To better comply with the intervention aims, the database was updated with sugar-sweetened foods/beverages and other processed foods frequent in Portuguese children’s diet and foods included in vegetarians and vegan diets (e.g., dairy and meat substitutes). The *SmartKidsDiet24* uses the child’s hand as a portion size tool [35] to estimate the food quantities and follows the recommendations for 24-h food recall dietary assessment implementation [36]. Parents are shown which meals have already been registered (e.g., green color instead of gray). When a meal is selected, parents have access to the list of foods previously added to that meal. When adding new foods, parents have two options: search by name (with auto-complete) or by food category. In the end, parents are asked if they want to continue adding others foods to that meal. They are also alerted to remember to add complementary items (e.g., chocolate in the milk). Data regarding the mean number of portions of vegetables, fruit, and sugar-sweetened foods and beverages registered on 3 days will be extracted from the database and analyzed separately as primary outcomes. Time points are as follows: baseline, immediately after the intervention, 3 months after the intervention, 6 months after the intervention.

##### Parental feeding practices

Parental feeding practices are evaluated through the *Food Parenting Practices Questionnaire* [37]. The questionnaire includes three main components: *Promotion of children’s intake self-regulation practices* (e.g., item 9: “If the child says he/she wants to eat more but I think the child had enough, I encourage him/her to stop eating.”), *Food availability and accessibility practices* (e.g., item 23: “I include some form of fruit in most meals*.*”), and *Ineffective control practices* (e.g., item 33: “I withhold sweets/dessert from my child in response to bad behavior.”). Parents answer the 40 items on a 5-point Likert scale (from *Totally false* to *Totally true*). Higher values on each scale indicate more frequent use of each type of practice. In an online study with parents of 2- to 5-year-old Portuguese children, the parental feeding subscales’ internal consistency ranged between 0.65 and 0.89, with an inter-item correlation mean (IICM) between 0.30 and 0.74 [37]. The three scores regarding *promotion of children’s intake self-regulation practices*, *food availability and accessibility practices*, and *ineffective control practices* are studied as primary outcomes. Time points are as follows: baseline, immediately after the intervention, 3 months after the intervention, 6 months after the intervention.

#### Secondary outcome measures

##### Parental perceived barriers related to food and feeding

Parental barriers are evaluated through the *Parental Perception on Children’s Healthy Feeding Barriers Questionnaire* [37], also developed for this study. The instrument includes 30 items organized in five subscales (*Child-related barriers*, *Parent-related barriers: vegetables & fruit*, *Parent-related barriers: added sugars*, *Context-related barriers, Cost-related barriers*). Parents answer on a 5-point Likert scale (from *Totally false* to *Totally true*). Higher values on each subscale indicate that the feeding barrier is more frequently identified. The subscales showed internal consistency scores between 0.66 and 0.95 and IICM between 0.25 and 0.90 [37]. Time points are as follows: baseline, immediately after the intervention, 3 months after the intervention, 6 months after the intervention.

##### Food parenting self-efficacy

To access food parenting self-efficacy, we used the *Parental Self-efficacy for Children’s Healthy Diet Scale* [38, 39]. The questionnaire aims to assess the extent to which parents are sure about their ability to promote the child’s intake of healthy foods and control the child’s intake of unhealthy foods, with four items answered on a 5-point Likert scale (from *No sure* to *Absolutely sure*). Higher values correspond to higher parental self-efficacy. The internal consistency of the instrument is acceptable (*α* = 0.74; IICM = 0.35) and has a good test-retest reliability (rs = 0.78, *p* > 0.01) [38, 39]. Time points are as follows: baseline, immediately after the intervention, 3 months after the intervention, 6 months after the intervention.

##### Parental motivation to change

Parental motivation to promote healthy changes in the child’s diet and parental feeding practices is measured through a set of three items answered in a 10-point numerical scale developed for this study and adapted from Rollnick et al. [40]. Each item evaluates a specific component of parental motivation: (i) the *importance* of participating in a program to help parents promote healthy eating patterns in children, (ii) the *confidence* to perform the proposed tasks and maintain engagement in the program, and (iii) the *readiness* to make changes in the child’s diet and their feeding behaviors. Higher mean scores indicate a higher motivation to change. The instrument showed an acceptable internal consistency (*α* = 0.76) in an intervention study with the ACT program that promoted positive parenting practices of children up to 8 years [41]. Time points are as follows: baseline, immediately after the intervention, 3 months after the intervention, 6 months after the intervention.

#### Other study variables

##### Sociodemographic information

Several parent and child variables are collected in the sociodemographic questionnaire (i.e., parents’ age and sex, level of education, kinship with the child, number of children and adults in the household, country of residency, and if parents receive child benefits). Parents also report specific information about their child: birth date, sex, childcare attendance, current professional support due to weight or eating problems, and the existence of chronic health or food intolerances and allergies. Time point is baseline.

##### Parent’s and child’s weight and height

Both parents’ and children’s weight and height measurements are self-reported. To increase parents’ report accuracy, the app shows specific instructions about assessing weight and height (e.g., in light clothing) correctly. The child’s BMI and percentile are calculated according to the WHO Child Growth Standards (BMI for age and sex). Time points are as follows: baseline, immediately after the intervention, 3 months after the intervention, 6 months after the intervention.

##### Perception of the child’s weight

Parents are asked to rate their child’s current weight subjectively, considering their age and height (underweight, average weight, overweight). Time point is baseline.

##### Concerns about the child’s weight

This dimension is assessed with the *Concern about the Child Weight* subscale of the *Child Feeding Questionnaire* — *Revised* [42] in its Portuguese version [43] and an additional question (i.e., *Considering your child’s height and age, please rate your concern about your child’s current weight*). All items are answered on a 5-point Likert scale (from *No concern* to *Very concerned*). Higher values in the subscale/item correspond to greater concerns about the child’s weight. The internal consistency of the Portuguese version was good (*α* = 0.87) [43]. Time point is baseline.

##### Child’s temperament

The temperament assessment was based on previous studies that identified several temperament clusters in preschool-aged children samples [44–47]. We retained the three temperament styles that seemed more consistent between studies: poor self-regulated or under controlled, inhibited or reactive, and easy or well-adjusted. Parents read three sentences that describe those temperament types and are asked to identify which better describe their child. Time point is baseline.

##### Application usability

To assess usability, we will use the System Usability Scale [48]. It is a commonly used, validated 10-item questionnaire that asks users to rate a system on a 5-point Likert scale from “1 = strongly disagree” to “5 = strongly agree.” Questions focus on the ease of use of the system and the integration of various functions within it. Time point is immediately after the intervention.

### Process evaluation

One of the benefits of a digital approach is the ability to instrument the application with logging capabilities, enabling quantification of usage, usability, and engagement. Our solution will be storing a record of timestamped user interactions, which would ultimately enable us to replay a timeline of actions. We are particularly interested in analyzing the number of accesses to the application and overall time; date and duration spent in each session, resource, and task; quality of the interaction in the interactive activities; the number of clicks and pages visited per session; and the number of notifications and time from notification to engagement.

### Data management

Considering that the RCT design includes repeated measurements, participants’ identification must be recorded to match data across time points. Data regarding the parents’ evaluation protocols, self-monitoring, or interaction with the app are associated with personal accounts. Only information relevant to the study is collected. Only one IT team researcher will access participants’ personal data (collected in the account registration) and unique identification codes. Online informed consent protocol includes a paragraph that explains which data will be recorded and how it will be saved. Parents are asked for permission for the research team to access this information, and to share relevant data with people from the Faculties taking part in the research, where needed. This trial does not involve collecting biological specimens for storage. All data will be stored in a password-protected secure study database. The host of the website will be the Amazon Web Services server. When the data collection has finished, the participant’s identification data will be destroyed, and data related to evaluation protocols and consent forms will be stored for 5 years in the same database.

We do not anticipate any problems that are detrimental to the participant and that require performing interim analyses or the definition of formal stopping rules for the trial. The Project Management Group will meet to review trial conduct once a month; a Data Monitoring Committee was not considered for this trial, as this is a low-risk intervention. The trial will be concluded when the estimated number of participants needed for this trial (*n* = 260) is reached. Any changes to the protocol will be notified by the PI to the sponsor and funder. Any deviations from the protocol will be fully documented using a breach report form. We will also update the protocol in the clinical trial registry.

### Statistical analysis

We will use intention-to-treat principles, with the participants being analyzed in the group in which they were allocated in the randomization process, independently of whether they had completed all measurement time points and/or the intervention. First, an evaluation of missing data mechanisms will be performed to inform which imputation strategy should be applied between multiple imputations (MI) and maximum likelihood estimation (FIML). Assuming the data are missing at random, a sensitivity analysis will be included, considering the whole samples vs. samples with complete data separately.

A descriptive analysis of demographic data and outcome variables at baseline will be performed for parents’ and children’s characterization purposes; the samples in each condition group will also be compared for all dimensions studied. Repeated measures analyses will be used to analyze the differences between condition groups and measurement time points over time regarding primary outcomes, adjusting for potential covariates. To study parents’ dropout predictors, we will first assess the differences between completers, early and late dropouts regarding demographic data, and all variables at baseline. The relationships between parents’ and children’s dimensions with dropout rates will be assessed. We will then conduct a binomial logistic regression to predict the overall dropout. The analysis of individual health trajectories regarding parents’ and children’s variables evolution throughout the intervention will be studied using mixed models. The *p* value will be corrected according to the number of primary outcomes considered in each statistical analysis.

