### Power and sample size

Statistical power analysis was performed for sample size estimation based on published data regarding this topic using G*Power 3.1.9.2. For our repeated measures within-between group comparison study, we used Cohen’s *f* criteria and considered a small effect size of 0.15 [8, 31], an alpha equal to 0.05, and power of 0.80 for a two-group with four repeated measures design (with a moderate correlation pattern between time measurements of 0.35). The sample size needed is approximately 130 participants (i.e., 65 parents in each of the two-arm groups), but the total sample size was adjusted to account for a dropout rate of 50% [32, 33]. Therefore, the sample will be collected until 130 participants in each group (*N* = 260) enroll in the study. Our proposed sample size will also be adequate for multilevel modeling with level 1 repeated measures nested within level 2 individuals, by assuring a minimum of 50 individuals required for level 2 [34].

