Possible limitations of our study protocol include the following: We anticipate most participants to be highly interested and motivated parents, with children with fewer feeding issues, possibly with a higher education level. We also expect most participants will be mothers. Although this is a common issue in parental nutrition interventions, children’s dietary patterns can be influenced by the other caregivers’ practices and the overall home food environment. Only the enrolled participant can complete the tasks and answer the questionnaires and food records. Also, all the measurement outcomes are reported by parents, including the objective measures (i.e., 24-h food recall, children’s and parents’ BMI), and those reports rule the self-regulatory strategies throughout the sessions. The RCT’s intervention arm is quite demanding due to the regular monitoring between sessions and the tasks required during the sessions. This experience can be challenging for some overwhelmed, time-constrained, or less motivated parents and might contribute to a high dropout rate. Also, a lack of direct contact with the research team can decrease parents’ involvement in the program. Although a design with an intervention arm and an active control condition comply with high-quality methodological standards, it also can lead to a less-expressive difference between conditions.

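### The mechanism check cannot choose between MI and FIML, and the stated complete-case comparison does not probe departures from missing at random

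*Protocol article*

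**What the plan says.** Under Statistical analysis, the article commits to intention-to-treat and then states that "an evaluation of missing data mechanisms will be performed to inform which imputation strategy should be applied", the candidates being MI and FIML. The next sentence takes MAR as its premise and says that "a sensitivity analysis will be included, considering the whole samples vs. samples with complete data separately". The section describes no other sensitivity analysis for missing outcomes. The dropout regression in the same section serves a separate objective: it relates dropout to baseline variables and is not linked to the efficacy estimate.

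Under Power and sample size, "The sample size needed is approximately 130 participants", and "the total sample size was adjusted to account for a dropout rate of 50" per cent, giving 130 per arm and 260 in total.

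The Discussion lists among the possible limitations that the intervention arm asks a lot of parents: "This experience can be challenging for some overwhelmed, time-constrained, or less motivated parents and might contribute to a high dropout rate". The Intervention section opens each new session only once the previous content and the between-session tasks are done. The Control condition section removes monitoring, goal setting and feedback from the comparator. Study design and Study procedures place the post-intervention assessment at the end of the program.

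**The concern.** Two things that the article fixes do not do the job they are given.

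First, the rule for choosing the method. If the evaluation points to data missing completely at random or to MAR, either method serves. If it points to MNAR, neither standard form does. There are good reasons to prefer one method, such as ease of using auxiliary variables or distributional form, but the type of mechanism is not one of them. Observed data also cannot separate MAR from MNAR.

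Second, the sensitivity analysis. Complete-case analysis generally needs a stronger assumption than MAR. Setting it beside a MAR analysis shows how much conditioning on observed data matters. It does not show what happens if dropouts differ from similar retained parents in ways not observed.

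With dropout budgeted at half the sample, the efficacy conclusion could rest heavily on MAR. A reader shown two similar estimates could take them as proof of robustness that they do not provide.

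**Working it through.** **Inputs from the protocol article.** Needed N 130, dropout 50%, enrolment 260, f = 0.15, correlation 0.35, four measures (Power and sample size); 1:1 allocation (Randomization process).

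**The plan's own figure.** 130 / (1 − 0.50) = 260, which matches. Nothing below changes this number.

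**Yardstick (assumed).** For two equal groups d = 2f, so f = 0.15 is read as 2 × 0.15 = 0.30 SD.

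**Step 1: dilution if intervention dropouts follow the control mean (assumed).** Suppose that dropout is unrelated to baseline and that control dropouts resemble control completers.
- Effect in all randomized = (1 − share missing in the intervention arm) × completer effect.
- At 50% missing: 0.50 × 0.30 = 0.15 SD.
- At 60% missing (not a figure from the article): 0.40 × 0.30 = 0.12 SD.
- Complete-case and MAR analyses would both stay near 0.30 SD, because nothing observed marks the dropouts as different.

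**Step 2: tipping point.** The shift in intervention dropouts that removes a 0.30 SD effect is 0.30 / dropout share.

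| Dropout in the intervention arm | Shift that removes the effect |
|---|---|
| 20% | 1.50 SD |
| 30% | 1.00 SD |
| 40% | 0.75 SD |
| 50% | 0.60 SD |

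The more dropout there is, the smaller the departure from MAR that suffices.

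**Step 3: does the whole-sample versus complete-case comparison signal the problem?** Simulation with 400,000 per arm, true effect zero, correlation 0.35 between waves, about 50% retained in each arm, and dropouts missing every post-baseline wave. Where retention is selective, its log-odds rise by 1 per SD of the variable named. The MAR-based estimate regresses the final outcome on baseline among retained parents in each arm and averages the predictions over all randomized in that arm, standing in for MI or FIML. The complete-case estimate is the unadjusted difference.

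| Retention depends on | Complete-case bias | MAR-based bias |
|---|---|---|
| Baseline, intervention arm only (MAR holds) | 0.15 SD | 0.00 SD |
| Unseen final outcome, intervention arm only (MNAR) | 0.41 SD | 0.37 SD |
| Unseen final outcome, both arms alike (MNAR) | 0.00 SD | 0.00 SD |

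In row 1 the two estimates disagree although MAR is true. In row 2 they nearly agree, and both are wrong by more than the 0.30 SD yardstick. In row 3 the biases cancel between the arms. So neither agreement nor disagreement tells the reader about MNAR, and the damage in this example comes from selection that differs by arm.

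**The case against.** The strongest reply is that this is a journal article, that an unseen analysis plan could add an MNAR analysis, and that the article does not call the complete-case comparison its only check. That stands as a limit: the point cannot be that an MNAR analysis is absent from the trial. It is that the article does fix a selection rule and a robustness check, and that neither serves its purpose.

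Several stronger readings are tempting and are not supported:
- *That the plan fails to test MAR.* No analysis of observed data can test it, including those proposed here. The fair statement is that the described check does not probe departures from it.
- *That half the outcomes will be missing.* The 50% is a planning allowance that the Discussion calls conservative, and the article describes reminders, a voucher and an active control to limit loss.
- *That the intervention arm will lose more parents.* The Discussion says only that its demands might contribute to dropout; no rate by arm is given.
- *That loss of less motivated parents is itself MNAR.* Motivation is measured at baseline and named as a dropout predictor, so such loss can be compatible with MAR once motivation is in the model.
- *That leaving MI or FIML open does serious harm.* With the same variables the two give nearly the same answer. Missingness can be examined without looking at treatment effects, and researchers are described as blinded. Learning which variables predict missingness may also reasonably favour MI, because it takes auxiliaries easily.
- *That the complete-case analysis is worthless or must go.* Row 1 of the simulation shows that it can reveal dependence on observed data.

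**Conclusion.** The point holds in a limited form. Choosing between two MAR methods by evaluating the mechanism has no sound basis, though its practical cost is small. The more important part is that the stated sensitivity analysis stays within MAR and cannot support a claim of robustness to MNAR. The article's own features make this worth correcting: a 50% dropout allowance, a heavier task load in one arm, and outcome collection placed after program completion. Together they make outcome-related, arm-unequal loss plausible, not established.

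The size is illustrative. Under the control-mean assumption, 0.30 SD among completers is 0.15 SD among all randomized at 50% loss. Under the simulated arm-specific MNAR pattern, both planned estimates are off by about 0.4 SD. These results rest on assumed dropout behaviour and on reading f = 0.15 as 0.30 SD; they do not estimate bias in this trial. The recommendation is a cheap improvement that could change how robust the conclusion is judged to be. It alters neither the sample size nor the data collected.

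**What to change.** 1. Name one primary method now and drop the mechanism check as the selector. Either a likelihood-based mixed model on all randomized parents, or MI by arm with the baseline dropout predictors already collected (for example education, motivation, self-efficacy, perceived barriers, temperament) as auxiliaries, would do.
2. Keep the complete-case analysis, labelled supplementary, and do not present its agreement with the main result as evidence of robustness.
3. Prespecify an MNAR sensitivity analysis for the primary outcomes: a delta-adjusted tipping-point analysis with shifts allowed to differ by arm, control-based MI, or both. Report the shift at which the conclusion changes and whether it is plausible.
4. Keep the dropout-predictor regression as a separate objective; its results can inform the auxiliaries but cannot stand in for step 3.

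Cost: a few sentences in the analysis plan and some programming, with no new data. The downside is that the robustness results may look less favourable than the complete-case comparison would.

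### State how the pre-randomization baseline enters the primary model: a group-by-time test with free baseline means would cost about a third to a half of the information at the plan's correlation of 0.35

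*Protocol article*

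**What the plan says.** The Abstract and the Study design section describe a two-arm trial with four repeated measures. The Abstract and the Outcome measures section list these as baseline, immediately after the intervention, and 3 and 6 months later. Under Randomization process and Study procedures, the baseline is completed before allocation.

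Power and sample size uses the same structure: "For our repeated measures within-between group comparison study, we used Cohen’s *f* criteria". Its inputs are "considered a small effect size of 0.15", "an alpha equal to 0.05, and power of 0.80", two groups with four measures, and "with a moderate correlation pattern between time measurements of 0.35". The result is about 130 evaluable parents (65 per arm), raised to 260 for 50% dropout. The section adds that this number would also suit multilevel modelling.

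The Statistical analysis section states for the primary comparison: "Repeated measures analyses will be used to analyze the differences between condition groups and measurement time points over time regarding primary outcomes". The same sentence goes on to allow adjustment for covariates, without naming them. The section leaves the choice between multiple imputation and full-information maximum likelihood open. It names mixed models only for trajectories during the intervention.

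**The concern.** Read together, these sections describe a group-by-time test over four occasions that include one the intervention cannot have affected. If each arm keeps its own baseline mean, every between-arm effect becomes a difference in change from baseline. Randomization makes the baseline means equal in expectation, so estimating a baseline difference between arms adds noise and gains nothing. With a correlation as low as 0.35 the noise is large: a change score varies more than the follow-up value alone.

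What is at stake is precision on all six primary outcomes (three dietary, three feeding-practice scores). The protocol expects 50% dropout, plans to correct the p value for the number of primary outcomes, and concedes in its Discussion that the active control may narrow the contrast between arms.

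**Working it through.** **Inputs.** From Power and sample size: f = 0.15, alpha = 0.05, power = 0.80, two groups, m = 4 occasions, correlation ρ = 0.35, 65 per arm. Assumed here: one common correlation (compound symmetry), SD = 1, complete data.

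**The plan's own figure.** For the within-between interaction, λ = f²·N·m·ε/(1 − ρ), with df 3ε and 3(N − 2)ε.
- With ε = 1, 80% power needs N = 82. At N = 130, λ = 0.0225 × 130 × 4/0.65 = 18 and power is 0.957.
- N = 130 (power 0.802) results with ε = 0.5. The article does not report that input; the value was found by working backwards. So 130 is not shown to be wrong, but it does not follow from the stated inputs alone.
- The dropout step reproduces: 130/(1 − 0.5) = 260.

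**One follow-up visit** (variance factor of the between-arm contrast).
- Free baseline means: 2(1 − ρ) = 2 × 0.65 = 1.30.
- Baseline ignored: 1.00.
- Baseline-adjusted: 1 − ρ² = 1 − 0.1225 = 0.8775.
- Information lost by free means against adjustment: 1 − 0.8775/1.30 = 32.5%.

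**Average of the three follow-ups.**
- Baseline ignored: (1 + 2ρ)/3 = 1.70/3 = 0.567.
- Free baseline means: 0.567 + 1 − 2ρ = 0.867.
- Baseline-adjusted: 0.567 − ρ² = 0.444.
- Information lost: 1 − 0.444/0.867 = 48.75%.

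**Check of the mechanism.** Generalized least squares on the 4 × 4 covariance matrix, with all four occasions as responses and baseline means constrained equal across arms, gives 0.8775 (single visit) and 0.444 (average). These equal the covariate-adjusted values. The loss therefore comes from letting baseline means differ by arm, not from having baseline among the responses.

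**Detectable difference**, 65 per arm, 80% power, two-sided 0.05: (1.960 + 0.842) × √(2/65 × variance factor).

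| Contrast | Free baseline means | Baseline-adjusted | n per arm, adjusted, for the free-means difference |
|---|---|---|---|
| Average of three | 0.457 SD | 0.328 SD | 34 instead of 65 |
| Single visit | 0.560 SD | 0.460 SD | 44 instead of 65 |

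**Other effect patterns**, 3-df test over the three follow-ups, share of noncentrality lost: constant 48.8%; 1/0.75/0.5, 42%; 0/0.5/1 or 1/0.5/0, 21%; last visit only, 10%.

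**Other correlations**, average and single visit: ρ = 0.2, 60% and 40%; ρ = 0.5, 37.5% and 25%; ρ = 0.7, 22.5% and 15%.

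**The case against.** The strongest reply is that the article never says baseline goes unadjusted. It gives no model equation, does not say whether baseline means are free or constrained, and allows covariates that could include the baseline outcome. A full analysis plan may settle this. That stands, so the point is conditional on the natural reading. Against it, the sizing method carries no baseline adjustment, and in a conventional repeated-measures analysis an occasion that serves as a response is not also a covariate.

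A second reply is that power is adequate at the plan's own effect. For a constant effect, f = 0.15 corresponds to 0.15/√0.046875 = 0.69 SD, and the group-by-time test then has power 0.957 at N = 130 with ε = 1. This also stands: the loss matters for smaller effects and for the width of the confidence intervals.

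A reader might go further in four ways that the documents do not support.
- *The plan discards half its information.* Half applies only to a sustained effect under the stated assumptions, and only if baseline means are free.
- *The trial has power of about 0.30.* That follows from assuming a constant 0.30 SD effect, which is f = √(0.09 × 0.046875) = 0.065, less than half the plan's 0.15.
- *The detectable effect falls from 0.54 to 0.33 SD.* That comparison mixes baseline adjustment with a move from a 3-df to a 1-df test. For the same averaged contrast the change is from 0.46 to 0.33.
- *The hypotheses cannot be tested because an omnibus interaction has no direction.* The article does not limit itself to an omnibus test, and its wording is compatible with time-specific contrasts.

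**Conclusion.** The point holds as one of efficiency; validity and type I error are not affected. If the primary model lets baseline means differ by arm, as the sizing and analysis wording suggest, it gives up about one third of the information at a single follow-up and about half for a sustained effect averaged over three. With non-constant effects the 3-df test loses 10% to 42%. Baseline adjustment was better in every pattern and at every correlation tried.

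The figures rest on ρ = 0.35 at every pair of occasions and on complete data. Unequal correlations, which a non-sphericity correction of 0.5 would imply, or the expected dropout would change the exact fractions.

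**What to change.** In Statistical analysis, state that each primary outcome is analysed with a longitudinal model of the three post-randomization assessments, with the outcome's baseline value as covariate and terms for arm, time and arm by time. A model of all four assessments with baseline means constrained equal across arms is an equivalent choice. Report the baseline-adjusted between-arm differences with confidence intervals.

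The sponsor should also name the primary contrast. An average over the follow-ups is more precise for a sustained effect but dilutes one confined to a single visit; a fixed time point does the reverse. That is the sponsor's choice, and the baseline adjustment is worth making either way.

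The cost is analysis wording only. Baseline is completed before allocation and the follow-ups are already scheduled, so no further data are needed.
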